***Blinding***

The Principal Investigator, Trial Statistician and members of the administration team, who input data from the study questionnaires, as well as the GPs, will be blinded to cluster allocation. The Trial Steering Committee and Data Monitoring Committee will also be blinded to cluster allocation unless it becomes absolutely necessary to reveal allocation.

## Sample size

In order to use the information recorded at all the time points we have considered the sample size needed to estimate the time-averaged difference in the pain response between the two arms. Diggle et al (2002) give the number of subjects needed per arm as M=2(z_α_ + z_β_)^2^{1+ (n-1)ρ}/(nΔ^2^), using a significance level of α, power 1-β, Δ= smallest meaningful difference in standard deviation units, n=number of repeated measures [63]. Given that the mean difference is expected to be zero at baseline, we will think of the effect size as an average of 0.2 over the three follow up time points. Using ρ=0.5 as an estimate of the autocorrelation, n=3, Δ=0.2, α=0.05, β=0.10, gives 350 per arm. To adjust for the clustering of the practices we modify this figure by the design effect (1+(m-1)*icc) for an average cluster size m. Using an icc=0.03, average cluster size of 30, the modified figure is 1309 leading to 44 practices to be recruited. Erring on the side of caution and adjusting for 25% non-response to the baseline questionnaire, 1745 patients will need to be screened and contacted; equivalent to approximately 40 patients per practice. Evidence suggests a consultation rate for OA and peripheral joint pain is at least 15 per month per typical GP practice, suggesting that the template will need to be active for approximately three months at each GP practice. If this poses logistical challenges, reducing the power to an acceptable 80% would result in 980 patients needed to be recruited from 34 practices with clusters of 30 patients (or 1307 to be screened and contacted across the 34 practices to allow for 25% non-response). The run-in period will further inform the estimate of non-response to the baseline questionnaire and if nescessary allow us modify the adjusted sample size needed.

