# *Statistical analysis*

Both the primary and secondary analysis will be by intention to treat and appropriate multiple imputation techniques will be used to account for missing data. The primary outcome, the current pain intensity component (0-10 numerical rating scale) of the Chronic Pain Grade [48], will be treated as interval in nature. Multilevel linear mixed modelling will be used to account for the clustered nature of the data. Using treatment by group interaction terms, differences in the mean response profiles will be investigated and quantified using appropriate 95% confidence intervals for the differences between intercept and gradient estimates.

Standard goodness of fit tests will be applied and if the distribution of the residuals is markedly non-normal, bootstrapping will be considered. Time varying covariates can also be accommodated within the multilevel framework.

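### The design effect also shrinks the between-practice variance by one third: if the ICC of 0.03 is for a single pain rating, 44 practices give about 83% to 86% power, not 90%, and the 34-practice fallback about 73% to 76%, not 80%

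*Protocol*

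**What the plan says.** All the figures are in the Sample size section of the protocol. The target is a difference averaged over follow-up: "we have considered the sample size needed to estimate the time-averaged difference in the pain response between the two arms". The formula for independent patients is M = 2(zα+zβ)²{1+(n−1)ρ}/(nΔ²) per arm, with its inputs defined as "Δ= smallest meaningful difference in standard deviation units, n=number of repeated measures". Then: "Using ρ=0.5 as an estimate of the autocorrelation, n=3, Δ=0.2, α=0.05, β=0.10, gives 350 per arm".

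Clustering enters in one further step, "To adjust for the clustering of the practices we modify this figure by the design effect (1+(m-1)*icc) for an average cluster size m", with the result: "Using an icc=0.03, average cluster size of 30, the modified figure is 1309 leading to 44 practices to be recruited". A smaller design is held in reserve: "reducing the power to an acceptable 80% would result in 980 patients needed to be recruited from 34 practices with clusters of 30 patients".

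The section gives no source for the 0.03. It does not say whether this is the ICC of one pain rating or of the mean of three ratings, nor how stable practice effects are assumed to be across visits. The Statistical analysis section says only: "Multilevel linear mixed modelling will be used to account for the clustered nature of the data".

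**The concern.** The factor {1+(n−1)ρ}/n = 2/3 describes how averaging three visits reduces the variance of a patient's score. It works by averaging out visit-to-visit variation. A practice effect that persists across visits is not averaged out. Multiplying the already reduced N by 1+(m−1)×icc treats the practice component as if it shrank in the same proportion, from 0.03 to 0.02 of the single-score variance.

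With 30 patients per practice, the practice component is a large part of the variance of a practice mean, so the step affects the power materially. At stake are the 90% claimed for the main design and the 80% that makes the fallback look acceptable. The Timeline in the GP-experience amendment shows the 8 practices of block 1 closing and 5 in block 2 active, so the choice between 44 and 34 practices could still have been open when that text was written.

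**Working it through.** **Inputs (Protocol, Sample size).** Δ = 0.2 SD, ρ = 0.5, n = 3, α = 0.05 (two-sided, since only that reproduces 350), power 90% or 80%, icc = 0.03, m = 30, 44 or 34 practices. Total variance of a single score is set to 1. Equal arms give 22 or 17 practices per arm.

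**The protocol's own figures reproduce.**
- 2(1.96+1.2816)² × 2/(3×0.04) = 350.2 per arm.
- Design effect 1+29×0.03 = 1.87; 2×350×1.87 = 1309; 1309/30 = 43.6, so 44 practices; 1309/0.75 = 1745.
- At 80% power: 262 per arm; 2×262×1.87 = 980; 980/0.75 = 1307.

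**What the product implies.** The variance of a practice mean (30 patients, three visits) becomes (2/3)×1.87/30 = 0.04156. This equals 0.02+(0.6667−0.02)/30, so the practice variance has been taken as 0.02. With 22 practices per arm, SE = √(2×0.04156/22) = 0.0615 and power = Φ(0.2/0.0615−1.96) = 90.2%.

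**Single-rating ICC with stable practice effects.** The practice variance stays at 0.03.
- ICC of the three-visit mean = 0.03/0.6667 = 0.045; design effect = 1+29×0.045 = 2.305.
- Variance of a practice mean = 0.03+(0.6667−0.03)/30 = 0.05122.
- 44 practices: SE = √(2×0.05122/22) = 0.0682; 0.2/0.0682 = 2.931; power = Φ(2.931−1.96) = 83.4% (81.7% with t on 42 df). A simulation of 20,000 trials, testing practice means with a t-test, gave 81.5%.
- 34 practices: SE = √(2×0.05122/17) = 0.0776; power 73.1% (70.5% with t on 32 df).
- N for 90% power: 700×2.305 = 1613.5, about 1614 patients in 54 practices. For 80%: 524×2.305 = about 1208.

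**Range over practice stability.** Let c be the correlation of practice effects between visits; the protocol gives no value. The practice variance of the three-visit mean is 0.03(1+2c)/3. Power, normal approximation:

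| c | Practice variance | 44 practices | 34 practices |
| --- | --- | --- | --- |
| 1.0 | 0.030 | 83.4% | 73.1% |
| 0.9 | 0.028 | 84.8% | 74.7% |
| 0.8 | 0.026 | 86.2% | 76.4% |
| 0.7 | 0.024 | 87.5% | 78.1% |
| 0.6 | 0.022 | 88.9% | 79.8% |
| 0.5 | 0.020 | 90.2% | 81.6% |

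The general design effect is 1+(m−1)×icc×{1+(n−1)c}/{1+(n−1)ρ}. It reduces to the protocol's 1.87 when c = ρ = 0.5, and equals 2.305 when c = 1.

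**ICC of 0.03 already on the three-visit mean.** The design effect of 1.87 is then right and power is 90.2%. The implied single-rating ICC, under stable practice effects, is 0.03×0.6667 = 0.02.

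**Slack elsewhere.** The 25% inflation covers only non-response at baseline. Rounding 43.6 practices up to 44 is already in the figures above.

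**The case against.** The strongest reply is that a design effect normally uses the ICC of the outcome whose N it inflates. The outcome here is the time average, and on that reading 1.87 is exact. The two factors also combine exactly if the one stated autocorrelation of 0.5 governs the whole response, practice component included. Every printed number reproduces, so nothing was miscalculated.

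This stands in part. A reader might infer that the 90% is simply false and that 83% is the true power. The documents do not support that. The 83% is the low end of the range tabulated above, and it needs a single-rating ICC with fully stable practice effects, neither of which the protocol states. A reader might also infer that the planned mixed model settles the matter by fixing a practice effect that is constant over time. It does not: the Statistical analysis section names no random-effects structure, the Primary objective speaks of growth curves, and such detail is commonly left to the SAP.

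What does not stand is the idea that the printed figures need no comment. Δ and ρ are both on the single-rating scale, so a bare ICC beside them reads most naturally on that scale too. A between-visit correlation of only 0.5 would make the average effect of a practice as changeable as one patient's pain rating, whose ρ of 0.5 includes that patient's own fluctuation and measurement noise.

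**Conclusion.** The concern holds in conditional form. The calculation shrinks the practice variance by one third without saying why. Under the natural reading, a single-rating ICC of 0.03, and between-visit practice correlations of 1.0 to 0.8, the main design has about 83% to 86% power and the fallback about 73% to 76%. With stable practice effects, the chance of missing the target effect is about 17% rather than 10% at 44 practices, and about 27% rather than 20% at 34. A t reference lowers the stable-practice figures to about 82% and 70%.

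These figures also assume equal practices of 30, complete follow-up and the time-averaged contrast as the one tested. The stated powers are right if 0.03 belongs to the three-visit mean. For a single-rating ICC they are reached only if practice effects correlate at about 0.5 or less (90%) or about 0.6 or less (80%) between visits. The fault is an undefined input and an unstated assumption, not a slip of arithmetic, and it does not by itself show that more practices must be recruited.

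**What to change.** State in the Sample size section which outcome the 0.03 refers to.

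- **If a single pain rating:** use the design effect 1+(m−1)×icc×n/{1+(n−1)ρ} = 2.305. Keep 44 practices of 30 and restate their power as about 83%, with a range of 83% to 86% for between-visit practice correlations of 1.0 to 0.8. Restate the 34-practice fallback as about 73% (73% to 76%) and stop describing it as 80%.
- **If the three-visit mean:** say so, and keep the printed figures.

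The cost is a recalculation and a few reworded sentences, with no extra patients or procedures. On the first reading, the stated power becomes less favourable.

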***Recruitment procedure***

*GP Practices*

Approximately 44 “Research Ready” GP practices that use the EMIS consultation system will be recruited through West Midlands Primary Care Research Network (PCRN) (North Cluster). Information given to practices will be general and they will be told that both arms of the trial will ask some questions that are not unlike those already asked as part of best practice primary care, e.g. assessment of pain intensity and depressive symptoms. Information divulged prior to randomisation will be minimal in order to reduce any bias in the practice deciding to take part as they will be told that they have an equal chance of being allocated to either the control or intervention arm. Practices will be selected on the basis of recent research activity, practice demographics and willingness to participate in the study. The GP practices involved in the study will include those from both urban and rural areas, different socio-economic groups and all sizes of practice (based on patient list size and number of GP partners).

When a practice has agreed to take part in the study, the set-up procedure in the practice will involve downloading anonymised patient information on consultation rates for OA, depression, anxiety, and the comorbid rates of these symptoms. An audit of access to psychological services will also be carried out to ensure that they have the resources to run the study adequately. Details of how practices will be randomised to the trial arms and the post-randomisation procedure are given below.

It is anticipated that the template will be active in each GP practice for approximately three months. GP practices will not all be recruited at once, rather recruitment will take place over a one year period and so the template will not be active in all practices at any one time. A service-level agreement will be ascertained with each GP practice, with a small reimbursement included to pay for practice time

*Patients*

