This component of the study involves semi-structured interviews with a sub-group of participating GPs. This interview schedule, which is based around the work of Coventry et al (2011) for screening for depressive symptoms in primary care patients with a long term health problem [65], is designed to complement the GP questionnaire, the responses to which will also contribute to the basis of the interview. GPs in the control arm were not asked to screen for depressive and anxiety symptoms, and therefore questions relating to the impact of screening for these symptoms on consultation time, doctor-patient communication and GP engagement will be limited to GPs in the intervention arm of the trial. However, those in the control arm will be asked their general views on the frequency and degree of presentation of such symptoms amongst their patients. In addition, both arms asked the question regarding pain intensity and so questions regarding the impact that this had will be included in the interview schedule for both arms. GPs from both arms of the trial will also be asked about the acceptability of screening in general for OA/joint pain patients and in how they have engaged with the study. The interview schedules are considered as topic guides for the interviews.

**Study participants:** It is anticipated that up to 40 interviews may be conducted, 20 from each arm. However, interviewing will continue until saturation is reached, i.e. no new themes are emerging from the process of on-going analysis. GPs will be sampled from those who have given their contact details in the GP questionnaire, ideally these will include GPs from practices that have screened the target number of patients, exceeded their screening target and screened less than target.

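### The sample size uses the equal-cluster design effect although recruitment per practice will vary, so the stated 90% and 80% power figures are somewhat optimistic

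*Protocol*

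**What the plan says.** The Sample size section starts from the "sample size needed to estimate the time-averaged difference in the pain response between the two arms". It then states: "Using ρ=0.5 as an estimate of the autocorrelation, n=3, Δ=0.2, α=0.05, β=0.10, gives 350 per arm". The clustering adjustment is the "design effect (1+(m-1)*icc) for an average cluster size m", and the result is given as: "Using an icc=0.03, average cluster size of 30, the modified figure is 1309 leading to 44 practices to be recruited". The only further inflation is for non-return of the first questionnaire: "adjusting for 25% non-response to the baseline questionnaire, 1745 patients will need to be screened and contacted". A reduced option at 80% power is "980 patients needed to be recruited from 34 practices with clusters of 30 patients". The run-in is to revise the non-response estimate; the section mentions no revision for cluster size.

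Elsewhere, the Recruitment procedure section says that the practices will include "all sizes of practice (based on patient list size and number of GP partners"), and that the template will be active for about three months in each. The nested GP substudy plans to interview GPs from "practices that have screened the target number of patients, exceeded their screening target and screened less than target". The Statistical analysis section specifies a multilevel linear mixed model.

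**The concern.** Putting an average cluster size into 1+(m-1)*icc leaves out the spread around that average. For a fixed total and a fixed number of practices, spread always lowers power, because patients added to a large practice bring less information than those missing from a small one.

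The protocol's own design creates spread. Practices differ in list size by intention, and the window is about the same length in each. It is derived from the consultation rate of a typical practice and is not scaled to list size. Patient numbers should therefore tend to follow list size, with differences in template completion and consent on top. The substudy text shows that practices above and below target are expected.

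At stake is whether the quoted 90% and 80% can be relied on. This matters most for the fallback, which starts almost exactly at the level the protocol calls acceptable.

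**Working it through.** **Inputs from the Sample size section:** alpha 0.05 (two-sided reproduces the stated figure), power 0.90, Δ = 0.2, n = 3, ρ = 0.5, icc = 0.03, average m = 30, 44 practices; fallback 980 patients in 34 practices.

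**Assumed:** the CV of cluster size, which the protocol does not give. I use 0.3 to 0.8. For scale, sizes spread evenly from 15 to 45 have a CV of 0.29; equal numbers of practices yielding 15, 30 and 45 have a CV of 0.41; sizes spread evenly from 5 to 55 have a CV of 0.48.

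**1. The protocol's figures.**
- Per arm: 2(1.960+1.282)² × {1+2×0.5} / (3×0.04) = 350.2, stated as 350.
- Design effect: 1+29×0.03 = 1.87. Total: 700×1.87 = 1309. Practices: 1309/30 = 43.6, so 44. Screened: 1309/0.75 = 1745.
- Fallback: the same formula at 80% power gives 261.6 per arm. Rounded up, 2×262×1.87 = 980.

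All of these patient numbers reproduce.

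**2. Margin with equal clusters.** With these inputs, power = Φ(√(N_eff/66.67) − 1.960), where N_eff is the total number of patients divided by the design effect.
- 1309 patients: N_eff = 700, power 90.0%.
- 44 × 30 = 1320 patients: N_eff = 705.9, power 90.2%.
- 980 patients in 34 practices (average 28.8, design effect 1.835): N_eff = 534.1, power 80.8%.

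**3. Unequal clusters, two methods.**
- (a) Unweighted design effect, a conservative bound: 1+((1+CV²)m−1)icc.
- (b) Weighting as in a mixed model: N_eff = Σ m_i/(1+(m_i−1)icc), with gamma-distributed sizes.

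Example, CV 0.5 and 44 practices averaging 30:
- (a) Design effect = 1+(1.25×30−1)×0.03 = 2.095; N_eff = 1320/2.095 = 630.1; power = Φ(3.074−1.960) = 86.7%.
- (b) A practice contributes 15.11 effective patients on average, against 30/1.87 = 16.04 with equal sizes; N_eff = 44×15.11 ≈ 664.8; power = Φ(3.158−1.960) = 88.5%.

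| CV | 44 practices, mean 30: mixed model | unweighted | 34 practices, 980 patients: mixed model | unweighted |
|---|---|---|---|---|
| 0 | 90.2% | 90.2% | 80.8% | 80.8% |
| 0.3 | 89.6% | 89.0% | 79.9% | 79.2% |
| 0.5 | 88.5% | 86.7% | 78.4% | 76.3% |
| 0.65 | 87.2% | 84.3% | 76.9% | 73.4% |
| 0.8 | 85.7% | 81.2% | 75.0% | 69.9% |

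With a full 34 × 30 = 1020 patients, mixed-model power is 81.6% with equal sizes, 80.1% at CV 0.4 and 79.3% at CV 0.5.

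**4. Practices needed to hold 90% at an average of 30** (mixed model / unweighted): CV 0.3, 45 / 46; CV 0.5, 47 / 49; CV 0.65, 49 / 53; CV 0.8, 51 / 58.

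**The case against.** The case on the other side has several parts.

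- **There is no calculation error.** The protocol speaks of an average cluster size and nowhere says that practices are equal. This stands: the point is an omitted allowance.
- **The size rests on a CV that the documents do not give.** This also stands. At CV 0.2, mixed-model power for 44 practices of 30 is still 89.9%.
- **The larger losses belong to an analysis that is not planned.** The protocol fixes a multilevel mixed model, so the mixed-model columns are the main figures and the unweighted ones only a bound. Even that bound leaves 44 practices above 80%. This stands.
- **The window is approximate and may be tied to a target.** The Run-in period section says that phase lasts until recruitment in its four practices is complete and only anticipates three months. Stopping at a count would narrow the spread. However, no such rule is written for the main phase, and the substudy text expects practices on both sides of target.
- **There may be slack.** The protocol's rate gives 15 × 3 × 0.75 = 33.75 responders per practice. If that held in 44 practices, mixed-model power would stay at 90% or more up to a CV of about 0.52. But the figure is before GP-applied exclusions and uncompleted templates, and the protocol itself plans on about 40 contacted and 30 recruited.
- **The fallback has a small margin of its own.** 980/30 = 32.7, so 34 full practices hold 80% up to a CV of about 0.4 under the mixed model. With the stated 980 patients the margin is gone by a CV of 0.3.

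**Conclusion.** The sample size omits variation in cluster size, which the protocol's own recruitment plan makes likely, and it leaves almost no margin to absorb it. The stated power is therefore somewhat optimistic. Under the planned mixed model and an assumed CV of 0.3 to 0.8, 44 practices averaging 30 give about 89.6% to 85.7%. The 34-practice fallback with 980 patients gives about 79.9% to 75.0%. The unweighted bounds are 89.0% to 81.2% and 79.2% to 69.9%. The fallback is the more exposed option, because a moderate spread takes it below the 80% that the protocol calls acceptable.

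A reader might infer that the arithmetic is wrong, or that the trial certainly lacks its stated power by a wide margin. The documents do not support either. The figures 350, 1309 and 1745 are correct, the CV is unknown, and with a small spread the loss is a fraction of a point. These results also take the protocol's icc, ρ and Δ as given, and they assume gamma-distributed cluster sizes for the mixed-model figures.

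**What to change.** In the Sample size section, state an assumed CV of recruited patients per practice and its source. Two sources are available: list sizes of the practices recruited so far, and recruitment counts from the four run-in practices. List sizes for all 44 practices are not at hand, because practices are randomised in successive blocks; the substudy timeline mentions 8 practices in block 1 and 5 in block 2.

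Give power with mixed-model weighting as the main figure and with 1+((1+CV²)m−1)icc as the conservative bound, for both 44 and 34 practices. Extend the run-in review to the spread of recruitment across practices as well as non-response.

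The cost is a sentence or two and a mixed-model power figure lower by roughly 1 to 5 points. No extra patients are required if that figure is accepted. Holding 90% at an average of 30 would instead take more practices, for example 47 (mixed model) to 49 (unweighted) at CV 0.5.

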***Mailing procedure***

An illustrated summary of the mailing procedure is provided in Figure 2. All eligible patients will be sent a study pack as outlined above. Those who do not respond within 2 weeks will be contacted again with a postcard reminder. At 4 weeks those who have not responded will be sent a second study pack and reminder letter. At baseline, patients who have still not responded at 8 weeks will be recorded as non-responders and will not be contacted again at any point in the study and their medical records will not be accessed. Participants who respond to the questionnaire but who do not consent to further contact, which will be specified on the consent form as being in 3, 6 and 12 months time, will also be recorded in the database as a non-consenting responder, ensuring that we do not contact them again in the future (this may occur by returning a completed or blank questionnaire or verbally by telephone conversation).

*Follow-up*

Participants who return a questionnaire and consent to participate at baseline will be sent a follow-up questionnaire at 3, 6 and 12 months following their index consultation. In order to maximise participation a short questionnaire, including only minimal data collection items (outlined below), will be sent to participants who have not responded to the full postal questionnaire at 6 weeks. At 6 and 12 month follow-up points an additional telephone call will be used at 8 weeks (for those participants who provided a telephone number in their baseline questionnaire) to attempt to contact non-responders in order to get information on their pain intensity at that time. Three telephone call attempts will be made to contact each participant. The mailing procedure is outline in Figure 2.

**Figure 2:** Mailing procedure

[figure not shown]

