***Run-in period***

An internal pilot of the trial protocol will take place in four practices, two in each arm. This “run-in” period will be used to ensure that our methods and key assumptions outlined in this protocol work successfully and that the day-to-day administration of the trial runs smoothly. Particular attention will be paid to the recruitment of GP practices, completion rate of the screening template, response rate to, and completion rate of the baseline postal questionnaire and the consent rate to further contact and medical record review. This phase of the trial will run until recruitment at these four practices is complete, which we anticipate to take three months. The template will not be activated in any further practices until this run-in period is complete. Data collected during this phase of the trial will be included in final data analysis as no interim analysis will be carried out with this data. Data from this phase of the trial will only be excluded from the final analysis if any substantial amendments to the current protocol have to be made.

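### The sample size allows for loss at baseline only, so the stated 90% power (and the 80% fall-back) holds only if follow-up at 3, 6 and 12 months is almost complete

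*Protocol*

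**What the plan says.** The Sample size section sets the target as follows: "we have considered the sample size needed to estimate the time-averaged difference in the pain response between the two arms". Baseline is not one of the repeated measures, because "we will think of the effect size as an average of 0.2 over the three follow up time points". The first result is for individual patients: "Using ρ=0.5 as an estimate of the autocorrelation, n=3, Δ=0.2, α=0.05, β=0.10, gives 350 per arm". It is then inflated for clustering: "Using an icc=0.03, average cluster size of 30, the modified figure is 1309 leading to 44 practices to be recruited". The last step is the only allowance for loss: "Erring on the side of caution and adjusting for 25% non-response to the baseline questionnaire, 1745 patients will need to be screened and contacted". The fall-back at 80% power (980 patients, 34 practices, 1307 contacted) is built in the same way, with the same 25%.

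Other sections of the protocol expect loss after baseline:

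- Mailing procedure provides a short questionnaire for those who have not answered the full one at 6 weeks. At 6 and 12 months, but not at 3, it adds telephone calls: "Three telephone call attempts will be made to contact each participant".
- Study administration and data storage provides for fortnightly checks for deaths and departures.
- Statistical analysis plans multiple imputation for missing data.

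Among the items that Run-in period singles out for attention is the "response rate to, and completion rate of the baseline postal questionnaire". It also names practice recruitment, template completion, and consent to further contact and record review.

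**The concern.** Dividing 1309 by 0.75 turns baseline responders into patients to contact. Nothing turns baseline responders into patients with follow-up scores, although the formula is built entirely on follow-up scores. The 25% cannot be read as general attrition, because the text ties it to the baseline questionnaire.

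The run-in does not close the gap. The update to the sample size that the protocol foresees concerns baseline non-response. The run-in phase ends when recruitment in its four practices is complete, expected after about three months, and response at later time points is not among the items it examines.

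At stake is the accuracy of the stated power. The section offers a choice between a 90% design and one at 80%, which it calls acceptable. Anyone choosing between them relies on two figures that hold only with near-complete postal follow-up over 12 months.

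**Working it through.** **Inputs, all from the Sample size section unless noted.** Two-sided α 0.05 (the section does not state sidedness; two-sided reproduces its 350, one-sided gives 285); power 90% or 80%; Δ = 0.2 SD; n = 3; ρ = 0.5; ICC 0.03; average cluster size 30; 44 or 34 practices. Allocation is 1:1 (Recruitment procedure: "they have an equal chance of being allocated to either the control or intervention arm"). The follow-up loss d is not given; 10%, 20% and 30% are assumed.

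**The plan's own figures.**

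- Per arm: 2(1.960 + 1.282)² × (1 + 2 × 0.5)/(3 × 0.04) = 350.2, stated as 350.
- Design effect: 1 + 29 × 0.03 = 1.87. Total: 700 × 1.87 = 1309.
- Practices: 1309/30 = 43.6, so 44.
- Contacted: 1309/0.75 = 1745.
- Fall-back: 261.6, rounded up to 262 per arm; 524 × 1.87 = 980; 980/0.75 = 1307.

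The patient and contact totals and the 44 practices reproduce. The fall-back's 34 practices are taken as stated (980/30 = 32.7).

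**Power formula.** In SD units the variance of a three-visit mean is (1 + 2 × 0.5)/3 = 0.667. With N patients in total and average cluster size m:

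- DE = 1 + (m − 1) × 0.03
- SE = √(4 × 0.667 × DE/N)
- power = Φ(0.2/SE − 1.96)

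Check at no loss: N = 1309, DE = 1.87, SE = 0.0617, 0.2/SE = 3.240, power = Φ(1.280) = 90.0%. Filling all 44 practices with 30 (N = 1320) gives 90.2%, so there is almost no slack.

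**With loss.** A fraction d gives no follow-up score. The number of practices stays fixed, so N becomes N(1 − d) and m shrinks in proportion.

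Main design, starting from 1309 in clusters of 30:

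| d | N | m | DE | 0.2/SE | power |
|---|---|---|---|---|---|
| 10% | 1178 | 27 | 1.78 | 3.151 | 88.3% |
| 20% | 1047 | 24 | 1.69 | 3.049 | 86.2% |
| 30% | 916 | 21 | 1.60 | 2.931 | 83.4% |

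Spreading the 1309 over 44 whole practices instead of 43.6 adds about 0.1 point.

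Fall-back, 980 over the stated 34 practices (980/34 = 28.8 per practice; 80.8% with no loss):

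| d | N | m | DE | 0.2/SE | power |
|---|---|---|---|---|---|
| 10% | 882 | 25.9 | 1.748 | 2.751 | 78.6% |
| 20% | 784 | 23.1 | 1.662 | 2.660 | 75.8% |
| 30% | 686 | 20.2 | 1.575 | 2.556 | 72.4% |

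The main design drops below 90% at a loss of about 1%, the fall-back below 80% at about 4%.

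**Partial records.** A patient with k of the three scores carries information k/(1 + (k − 1) × 0.5), against 1.5 for a complete patient. Suppose response at 3, 6 and 12 months is 90%, 85% and 80%, and those who drop out do not return. The retained fraction is (0.80 × 1.5 + 0.05 × 1.333 + 0.05 × 1)/1.5 = 0.878, and power is about 88%. With 80%, 75% and 70% the fraction is 0.778 and power about 86%.

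**The case against.** The strongest reply is that the shortfall is modest. Across the assumed range the main design stays above 80%, the level the protocol itself calls acceptable. Reminders, short questionnaires and telephone calls all collect the primary outcome, so fewer patients will miss every wave than will miss any one wave, and a mixed model uses what they give. The planned 95% confidence intervals will show the precision actually achieved, whatever power was stated beforehand. All this stands, and it limits the severity. It does not make the stated power right: imputation and mixed models use the available information but do not replace what was never collected.

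There may also be unused slack. Pain is recorded at consultation and at baseline. If an earlier score correlated 0.5 with the later ones were adjusted for, the variance would fall from 0.667 to 0.667 − 0.25 = 0.417. With the practice component held at 0.03 × 0.667 = 0.02, power at 20% loss would be about 93%. But Sample size takes no credit for this and Statistical analysis does not specify it, so it is a possibility and not a property of the plan.

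Three stronger readings are tempting, and the document does not support them:

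- **That the calculation is arithmetically wrong.** It is not; the totals follow from the stated inputs.
- **That 0.03 is the ICC of a single score, so that 0.03/0.667 = 0.045 should apply to the three-visit mean.** The protocol applies 0.03 directly to the time-averaged sample size and does not say that it refers to a single score. Reading it as the ICC of the mean is equally open.
- **That the run-in looks at baseline response alone.** It also checks template completion and consent to further contact, which decides who enters follow-up. What it omits is response once follow-up has begun.

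**Conclusion.** The point holds as a planning-assumption error of moderate weight. The protocol states 90% and 80% power for numbers of baseline responders, and both figures require virtually complete follow-up, which its own procedures do not expect.

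For 10% to 30% loss the main design loses about 2 to 7 points, and the fall-back lands about 1 to 8 points below its stated 80%. These sizes rest on the assumed loss range, on fixed numbers of practices, on the plan's own ρ and ICC, and on lost patients giving no follow-up score at all. Where patients give some scores the shortfall is smaller.

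The fall-back is the more exposed option, because even a small loss takes it below the level at which it is offered. A reader should not infer that the trial is badly underpowered or must enrol more patients. A statistical analysis plan not seen here does not change the point, since the protocol itself states the sample size, its only adjustment and its power.

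**What to change.** In the Sample size section, add an assumed rate of loss between baseline and the follow-up questionnaires, with its basis, and restate the power that 1309 responders in 44 practices and 980 in 34 practices deliver at that rate. At an assumed 20%, for example, these would be about 86% and 76%. If the sponsor wants credit for partial records, state the response pattern assumed at each time point.

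No extra enrolment is needed to correct the statement. The cost is one paragraph and a stated power a few points lower.
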